**Methods:**

Nov-RPM-HF is a 100-patient single-center prospective trial, evaluating patients over 6 months. The outcomes will include patient adherence to data collection, patient/clinician-perceived utility of the RPM platform, medication changes including the titration of guideline-directed medical therapy to target doses, heart failure symptoms/performance status, and unplanned heart failure hospitalizations or emergency department visits.

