##### Medication Changes

Clinician-directed changes will be tracked during trial duration for the following HF medication classes: beta-blockers, angio-converting enzyme (ACE)/angiotensin receptor blocker (ARB)/angiotensin receptor-neprilysin inhibitors (ARNIs), magnetic resonance angiographies (MRAs), hydralazine, nitrates, and loop diuretics. The distance to target dose will also be assessed for GDMT medications, beta-blocker, ACE/ARB/ARNI, and MRA drug classes. Based on previously established methodology [10], baseline doses of each of these drug classes will be the classified percentage of target dose: 0% to 25%, 25% to 50%, 50% to 75%, and 75% to 100%. This target dose category will be compared for each participant between 0 and 6 months to assess for changes in GDMT dosing. Change in proximity to target dose over trial duration will be compared to that of matched controls (see “Statistical Considerations” for matching methodology). For all drug classes, the absolute number of medication changes will be recorded and compared to that of the matched controls.

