#### Statistical Analysis

Patient medication changes and clinical events will be compared to 100 matched historical controls. Controls will be patients with HFrEF matched on an HF hospitalization in the past year, age within 5 years, sex, race, and comorbidities (coronary artery disease, diabetes mellitus, hypertension, renal disease).

Statistical analysis for clinical end points will be in comparison with matched controls. For survey data, including RPM platform utility and patient symptom assessments, these will be evaluated for change over the trial’s 6-month duration. Continuous variables will be assessed via sample *t* tests, and categorical variables will be assessed via chi-square tests.

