A lack of clinically actionable RPM alerts has been commonly observed in prior noninvasive RPM studies. A systematic review of noninvasive RPM trial clinical alerts revealed patients were contacted only 39% (range 29%-52%) for follow-up and management changes [14]. Furthermore, RPM alerts with high false-positive rates have previously led to unnecessary office visits and hospitalizations [23]. Nov-RPM-HF will assess clinical utility of all absolute threshold alerts based on if there is a corresponding clinical action. Alert utility will be broken down by alert type (weight, BP, HR) to assess comparative utility of each physiologic measure.

Although seldom measured in RPM clinical trials, adoption and buy-in from the clinical team is essential for maximal and effective RPM use. Factors affecting clinical adoption include perceived utility of RPM-provided patient data and integration into existing clinical workflows [15]. Nov-RPM-HF evaluates a clinician-designed RPM platform, and clinical utility will be assessed through structured surveys, broken down by RPM platform components, and evaluation of clinical actions motivated by RPM alerts.

Nov-RPM-HF will provide an important contribution to the field of RPM for patients with HFrEF. Its design attempts to overcome prior limitations of prior RPM strategies and determine its impact on patient engagement and satisfaction, clinical satisfaction, and HF medical optimization. Insights from the study will inform the future role of noninvasive RPM as a viable HF clinical management strategy.

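### The plan names chi-square for categorical data, but the 0 versus 6 month target-dose category is paired and ordered, and an ordinary chi-square would miss most real shifts

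*Protocol article*

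**What the plan says.** The Statistical Analysis section gives a single sentence on test choice. Continuous variables get t tests and "categorical variables will be assessed via chi-square tests". It names no paired, ordinal, matched or clustered version.

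Under Outcomes, Medication Changes, the dose of each guideline-directed drug class is "classified percentage of target dose: 0% to 25%, 25% to 50%, 50% to 75%, and 75% to 100" percent, which makes four ordered levels. Two comparisons are planned:

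- Within patient: "This target dose category will be compared for each participant between 0 and 6 months to assess for changes in GDMT dosing".
- Between groups: "Change in proximity to target dose over trial duration will be compared to that of matched controls".

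The abstract gives the size and follow-up: "Nov-RPM-HF is a 100-patient single-center prospective trial, evaluating patients over 6 months". For the control group, the Statistical Analysis section says "Patient medication changes and clinical events will be compared to 100 matched historical controls", and the matching factors are HF hospitalization in the past year, age, sex, race and comorbidities.

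For alerts, Outcomes defines utility as the percentage of absolute threshold alerts that led to clinical action, by physiologic measure. The Discussion adds: "Alert utility will be broken down by alert type (weight, BP, HR) to assess comparative utility of each physiologic measure". Neither place names a test.

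**The concern.** Pearson's chi-square compares independent samples. At 0 and 6 months the same people are classified twice, and most of them will be in the same category both times. The test takes its standard error from two unrelated groups of 100, which is far too large for the difference between two strongly correlated distributions. It also spends three degrees of freedom on any difference in shape, when the question is whether doses moved up.

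Optimizing guideline-directed therapy is a stated aim of the trial (Introduction; Methods, Overview). If the written rule is followed literally, a clear rise in dose category would most likely be reported as no change.

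**Working it through.** **The plan's own paired figure.** The article gives no power for dose category. The nearest stated figure is 84% power for a 6-point KCCQ change with SD 20 (Power Calculation, HF Symptoms and Performance Status). With n = 100 and two-sided alpha 0.05, a one-sample (paired-difference) t test has noncentrality 6/(20/√100) = 3 and power 84.4%, so the figure reproduces. Two independent groups of 100 would give 56.4%. The plan therefore relies on within-patient analysis for KCCQ, while its rule for categorical data does not mention pairing.

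**Dose category: inputs.** From the article: n = 100 and four ordered levels. Assumed, because the article does not give them: the baseline distribution, the shares moving one level up or down, and no missing 6-month data. A patient in the top level cannot move up, and one in the bottom level cannot move down.

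**Expected counts by hand.** Baseline 35/30/20/15; 20% up, 5% down.

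- Expected 6-month counts: 29.5/30.5/21.75/18.25.
- Ordinary chi-square for two equal samples is Σ(a−b)²/(a+b) = 0.469 + 0.004 + 0.073 + 0.318 = 0.86 on 3 df. The 5% critical value is 7.81, so p is about 0.83.
- Sign test: up-moves 0.20 × 85 = 17; down-moves 0.05 × 65 = 3.25; z = (17 − 3.25)/√20.25 = 13.75/4.5 = 3.06.

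With 30% up and 5% down, the chi-square is 1.33 + 0.02 + 0.18 + 0.78 = 2.30 (p about 0.51). The sign test gives (25.5 − 3.25)/√28.75 = 4.15.

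**Simulation** (20,000 trials per row; share of trials with p < 0.05):

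| Assumed baseline (%) | Up/down (%) | Ordinary chi-square | Exact sign test |
|---|---|---|---|
| 35/30/20/15 | 20/5 | 0.1% | 86% |
| 35/30/20/15 | 30/5 | 2.1% | 99% |
| 40/25/20/15 | 20/5 | 0.3% | 88% |
| 40/25/20/15 | 30/5 | 5.7% | 99.6% |
| 25/25/25/25 | 20/5 | 0.03% | 71% |
| 25/25/25/25 | 30/5 | 0.9% | 97% |
| 25/25/25/25 | 10/10 (no net change) | 0.0% | 2.6% |

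The last row shows the cause: the nominal 5% chi-square almost never rejects under no change. The result does not depend on choosing the sign test. Stuart-Maxwell, which is paired but ignores order, gave 55–77% at 20/5 and 92–98% at 30/5 for the last two baselines.

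**Where the loss is smaller.** If the scale were cut in two, chi-square against McNemar would be 2% against 70% when 8% cross upward and 1% downward, but 90% against 98% at 25% and 5%. The article specifies four levels.

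**Matched controls.** Suppose 40% against 22% are up-titrated in 100 pairs (assumed). Chi-square has about 80% power and McNemar 79% when the pairs are uncorrelated. At a pair correlation of about 0.3 the figures are 84% and 92%. The loss is 0 to about 8 points, and the chi-square type I error falls from 5.2% to 2.0%.

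**The case against.** The strongest reply is that one generic sentence in a condensed article may cover the paired forms. McNemar and Stuart-Maxwell are themselves chi-square tests, the KCCQ power shows that the generic t test includes a paired one, and the dose category is to be compared participant by participant. This makes it plausible that a paired analysis is intended. It does not settle the matter: no paired form is named, the rule read plainly gives the wrong test, and even the paired chi-square variants for four levels ignore the ordering.

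Three stronger readings are tempting, and the article does not support them.

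- *All dose comparisons lose their power.* The comparison of change with matched controls keeps nearly all of it. If a change category is formed for each patient and then compared between groups, chi-square is close to valid.
- *Ignoring the matching is a serious error.* The plan says "Statistical analysis for clinical end points will be in comparison with matched controls" and names no matched method, but the effect is mild conservatism. The medication-change count is powered under a Poisson assumption, so chi-square is not clearly its test.
- *The alert comparison has inflated error of known size.* No test is tied to alerts, and a descriptive breakdown would satisfy the text. A reader might apply the design effect 1 + (m−1) × ICC and obtain an actual error of 10% (5 alerts, ICC 0.1) to 45% (20 alerts, ICC 0.3). That formula assumes that the compared groups contain different patients. Here the same patients produce weight, BP and HR alerts, so a shared patient effect partly cancels. In null simulations, a chi-square on pooled alerts rejected in 1–5% of runs when the patient effect was shared and alert counts were similar across types. It rejected in up to about 65% when effects or counts varied independently by type. The direction and size of the error are unknown.

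**Conclusion.** The point holds for the within-patient 0 versus 6 month comparison of target-dose category. The test as written does not fit paired, ordered data. For shifts of 20–30% up and 5% down in 100 patients, it would detect a change in about 0–2% of trials under two of the assumed baselines, and in up to about 6% under the third. A paired sign test would detect it in about 71–99%. The exact percentages rest on assumed baselines, one-level moves and complete data. The severe conservatism itself comes from ignoring the pairing and appears under all three baselines. Matching and alert clustering are secondary: the first is a modest loss of efficiency, and the second matters only if alert types are formally tested.

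**What to change.** State in the analysis plan that the 0 versus 6 month target-dose category will be tested within patient, by drug class, with a paired ordinal method: Wilcoxon signed-rank or sign test, or a mixed ordinal model. Stuart-Maxwell is acceptable if ordering is deliberately set aside.

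Two smaller additions:

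- For participant-versus-control comparisons, account for the matched sets with a paired or conditional test, or with regression clustered on the matched set.
- Say whether the alert breakdown is descriptive. If alert types are to be formally compared, use GEE or a bootstrap that resamples patients.

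The cost is a few sentences and slightly more analysis work. No new data or patients are needed.

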#### Power Calculation

##### Medication Changes

This trial is powered at 99% to assess for 50% more medication changes in the study arm compared to historical controls. We will use a type I error of 0.05, assuming Poisson distribution [17]. This medication change rate was selected based on prior work in the CHAMPION trial, in which monitored patients had over double the number of medication changes (n=2468 for 270 patients vs n=1061 for 280 patients; *P*<.001) [18].

##### HF Symptoms and Performance Status

This trial is powered at 84% to assess for a 6-point increase (SD 20) in KCCQ scores for trial participants over the trial duration. We will use a type I error of 0.05. This improvement in KCCQ scores was based on the Minnesota Living with Heart Failure symptom assessments improvements observed in the CHAMPION trial [19].

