### Study Protocol

Following enrollment, study participants have the Home Hub and sensors shipped to their homes. Once the kit is delivered, the technical support team will reach out to assist with home monitoring and sensor setup.

As part of the study, patients will take measurements daily from all study sensors. The first 7 days for each patient will be a run-in period where patient data is collected. If sufficient data is collected and transmitted, study participants will transition to the active management phase. Sufficient data is defined as transmission from both BP cuff/weight scale and ballistocardiograph sensors in at least 4 of the 7 days. If minimum requirements are not met, patients are continued in the run-in period for an additional week (up to 3 weeks maximum). Technical support will contact patients to determine if lack of transmission represents a technical issue versus nonadherence. If patients were unable to meet minimum data requirements after 3 weeks, then they were disenrolled from the study.

Following run-in period completion, study participants will enter the 6-month active management phase of the study. A designated research nurse is responsible for daily monitoring of the RPM clinical interface. This includes monitoring the RPM clinical interface daily for clinical alerts, contacting patients to assess clinical status in response to alerts, and escalating to the patient’s HF cardiologist if clinical status warrants management changes. This research nurse will also be responsible for contacting study participants for issues with data transmission or poor adherence to patient data collection.

On a monthly basis, enrolled patients will have their clinical data reviewed by a multidisciplinary team including a triaging nurse and an HF cardiologist. The purpose of these reviews is to assess participant’s clinical status and adherence to data transmissions, and to identify opportunities for optimized medical management, including maximizing GDMT. RPM platform monitoring is outlined in Figure 2.

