##### HF Symptoms and Performance Status

Study participants’ symptoms and performance status will be evaluated using the Kansas City Cardiomyopathy Questionnaire (KCCQ-12) at 0, 3, and 6 months (Multimedia Appendix 1), with absolute results and change over study duration reported.

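### The 84% KCCQ power allows for essentially no loss of patients, and the uncontrolled before-after change it refers to cannot be read as an effect of remote monitoring

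*Protocol article*

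**What the plan says.** The abstract gives the size: "Nov-RPM-HF is a 100-patient single-center prospective trial, evaluating patients over 6 months". Under Power Calculation, HF Symptoms and Performance Status, the article states "This trial is powered at 84% to assess for a 6-point increase (SD 20) in KCCQ scores for trial participants over the trial duration" and adds "We will use a type I error of 0.05". It does not give the sidedness of the test or say whether 20 is the SD of the change or of a single score.

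Under Outcomes, KCCQ-12 is scheduled for study participants "at 0, 3, and 6 months". Statistical Analysis says "For survey data, including RPM platform utility and patient symptom assessments, these will be evaluated for change over the trial’s 6-month duration" and assigns t tests to continuous variables. The same section uses the 100 matched historical controls for medication changes and clinical events, so KCCQ has no comparator.

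Study Protocol places the run-in after enrolment, with a minimum data requirement and up to 3 weeks to meet it. For patients who still fall short: "If patients were unable to meet minimum data requirements after 3 weeks, then they were disenrolled from the study". The 6-month active management phase follows. Textbox 1 requires NYHA class II-IV and a heart failure hospitalization or ED visit in the last 12 months. The Overview says this was done to obtain a population with a higher event rate.

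**The concern.** Two questions arise from one sentence of the power section.

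The first is how many patients the 84% assumes. A paired comparison of 0 and 6 months uses only patients with both scores. If the figure needs all 100, any run-in failure counted within the 100, and any death, withdrawal or missed 6-month questionnaire, takes the trial below its stated power.

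The second is what a significant result would mean. All patients enter with a heart failure event in the past year, and all attend a clinic that, by the article's account, focuses on implementing guideline-directed therapy. Symptom scores may rise over 6 months without any contribution from the platform. With no control group for KCCQ, a rise could be credited to remote monitoring when the design cannot show that.

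**Working it through.** **Inputs.** Mean change δ = 6, SD = 20, type I error 0.05 (power section); n = 100 (abstract); within-patient change over 6 months by t test (Statistical Analysis). Two-sidedness and 20 as the SD of the change are my assumptions, tested below.

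**Reproducing 84%.** For a paired (one-sample) t test the noncentrality is λ = δ√n / SD, with n − 1 degrees of freedom. Power is the probability that a noncentral t variable falls outside ± t(0.975, n − 1).

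- n = 100: λ = 6 × 10 / 20 = 3.00; power = 84.4%, which matches.
- Normal approximation, n = 100: Φ(3.00 − 1.96) = 85.1%, close but one point higher.
- One-sided t test, n = 100: 90.9%, which does not match.

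**How many pairs 84% implies.** With the t test, 100, 99 and 98 pairs give 84.4%, 84.0% and 83.7%. With the normal approximation, 98, 97 and 96 pairs give 84.4%, 84.0% and 83.6%. Either way the figure leaves room for the loss of at most about four patients in 100.

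**Power over a range of losses.** The article gives no loss rate, so 0 to 30% is an assumption. Two-sided paired t test, δ = 6, SD of change 20:

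| Complete 0/6-month pairs | Assumed loss from 100 | λ = 6√n / 20 | Power |
|---|---|---|---|
| 100 | 0% | 3.00 | 84.4% |
| 95 | 5% | 2.92 | 82.5% |
| 90 | 10% | 2.85 | 80.4% |
| 85 | 15% | 2.77 | 78.1% |
| 80 | 20% | 2.68 | 75.5% |
| 70 | 30% | 2.51 | 69.7% |

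The smallest number of pairs giving 80% is 90.

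**Dependence on what SD 20 means.** If 20 were the SD of a single score and ρ the correlation between the 0- and 6-month scores, the SD of the change would be 20√(2(1 − ρ)). With 100 pairs:

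- ρ = 0.3: SD of change 23.7, power 71%
- ρ = 0.5: SD of change 20.0, power 84.4%
- ρ = 0.7: SD of change 15.5, power 97%

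So the stated 84% holds if 20 is the SD of the change, or if it is a single-score SD and the correlation happens to be 0.5. The article should say which it means.

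**Attribution.** No arithmetic applies here. Statistical Analysis gives controls to medication changes and clinical events only. Textbox 1 makes a heart failure event in the prior 12 months a condition of entry. The mean 0-to-6-month change in this single group is the sum of any platform effect, recovery after the event, regression to the mean and ordinary clinic care. Nothing in the design separates these parts.

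**The case against.** The strongest reply is that the figure is right. It reproduces from the stated inputs, and the loss is modest: power stays at or above 80% until more than 10 of 100 pairs are gone. The article does not say whether the 100 are counted before or after run-in, or whether disenrolled patients are replaced, and a fuller protocol may settle this. If 100 patients enter active management, the run-in rule costs no power and only later losses count. The article also describes KCCQ as change in participants and, in its list of aims, uses the word impact for medication changes and clinical outcomes. All of this stands, and it limits the point to a best-case figure that should be labelled as one.

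A reader might also infer several stronger things that the documents do not support:

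- *That 84% is an arithmetic error, or that the disenrolment rule makes 100 pairs unlikely.* The figure reproduces, and no failure rate is given. Some loss is foreseeable; its size is unknown.
- *That the test is unpaired, with far lower power.* The Outcomes and Statistical Analysis sections both describe change over the study, which is a within-patient analysis.
- *That dropout must push the mean change up.* A lost patient leaves both time points of a paired analysis. The mean rises only if that patient's unseen change would have been below average, and nothing shows this.
- *That the 6-point target was carried over from the Minnesota questionnaire without conversion.* The article says only that the target was based on those results. The derivation cannot be judged without the cited source.
- *That splitting patients by time since the qualifying event would isolate a platform effect.* The documents offer no basis for a cut-off, and no split within a single arm supplies a control.

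**Conclusion.** The point holds as a moderate one. The 84% is correct arithmetic for a case with essentially no attrition, in a plan where loss is foreseeable: run-in follows enrolment, and patients chosen for a high event rate are followed for 6 months. The cost runs from about 2 percentage points at 5% loss (84.4% to 82.5%) to about 15 points at 30% (84.4% to 69.7%). These sizes rest on an assumed loss range, a two-sided test, and 20 as the SD of the change.

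The question of interpretation matters more than the power and does not depend on any loss rate. Without a KCCQ comparator, and with entry conditional on a recent event, a significant rise shows that scores changed during monitoring. It does not show that monitoring changed them. Equally, the documents do not show that scores would have risen without the platform; the design leaves the question open.

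**What to change.** 1. In the KCCQ power paragraph, state that 20 is the SD of the change (or correct this if it is not), that the test is two-sided, and whether the 100 are counted before or after run-in. Give power over a range of losses: 84.4%, 82.5%, 80.4%, 75.5% and 69.7% for 100, 95, 90, 80 and 70 complete pairs.
2. In Statistical Analysis, replace the t test on the 0-to-6-month KCCQ change with a repeated-measures mixed model. Include the 0-, 3- and 6-month scores of all participants with a baseline score, and take the 6-month-minus-baseline contrast as the estimate. A patient with a 3-month but no 6-month score then still contributes. The model assumes that missingness is explained by the observed scores, and this should be stated.
3. Report the KCCQ result as change during monitoring, not as an effect of the platform, and name recovery, regression to the mean and usual care as explanations the design cannot exclude.

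The cost is a slightly lower stated power and a little more analysis work. The three KCCQ assessments are already scheduled, so no visits or questionnaires are added.
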